### Plans to promote participant retention and complete follow-up {18b}

Throughout the recruitment and follow-up period, retention has been constantly assessed by the trial management group including patient representatives. A participant diary is provided to participants to aid data collection at 6 months and each participant receives a phone call from research team at day 30 and at 6 months. A voucher of nominal value is posted out to participants as a thank you for their participation.

### Data management {19}

Personal data collected during the trial will be handled and stored in accordance with the 2018 Data Protection Act. Participants will be identified using unique trial number only, and no data which identifies participants by name will be shared with nor held at Warwick CTU.

We will use the standard WCTU trial web-based application for data management. Participant data (including case report forms) will be collected in accordance with the protocol from PQIP database. Clinical data will be collected during the hospital stay up to 30 days after randomisation. Baseline characteristics collected include participant demographics, comorbidities, pre-admission function, quality of life, inclusion/exclusion criteria, consent, surgical speciality, expected duration of surgery, time and date of randomisation. Data captured following randomisation will include administered anaesthetic techniques, post-operative complications, participant satisfaction, quality and speed of recovery, accidental awareness, health resource use, health-related quality of life, SAEs and survival status.

The case report form (CRF) has been developed by the WCTU in conjunction with PQIP and made available to the participating sites as a paper and electronic CRF (eCRF) for ease of data collection; supporting materials will be available to staff. On all trial-specific documents, other than the signed consent form, the participant will be referred to by a unique trial-specific number in any database, not by name. Signed consent forms will be retained at the recruiting site and will not be shared with WCTU. The trial will be conducted in accordance with the current approved protocol, Good Clinical Practice (GCP), relevant data protection regulations, the trial data management plan, and WCTU standard operating procedures (SOPs). A monitoring plan and risk assessment will be devised to protect participant safety and integrity of trial data.

### Database

The VITAL database will be developed by the Programming Team at WCTU and will link by unique identifiers to the PQIP database. All specifications (i.e. database variables, validation checks, screens) will be agreed between the programmer and appropriate trial staff. For further information regarding the PQIP database, please refer to PQIP study information (www.pqip.org.uk).

### Data storage

All essential documentation and trial records will be stored by WCTU in conformance with the applicable regulatory requirements, and access to stored information will be restricted to authorised personnel. Any paper data forms will be stored in a lockable filing cabinet in a secure room, to which access is restricted to authorised personnel. Electronic data will be stored in a secure area of the computer with access restricted to staff working on the trial and the WCTU Quality Assurance team. All databases containing identifiable information will be encrypted and password protected. Any data that are transferred out of the secure environment will adhere to WCTU SOPs.

### Data access and quality assurance

All data access will be controlled by individual usernames and passwords, and any changes to data will require the user to enter their username and password as an electronic signature in accordance with regulatory requirements. Staff will have access restricted to the functionality and data that are appropriate for their role in the trial and will not share their log in details.

### Data shared with third parties

Any data transfer would be in accordance with University of Warwick SOPs and require data sharing/processing agreements to be in place prior to transfer.

### Archiving

Trial documentation and data will be archived for at least ten years after completion of the trial. Trial Master File and associated data will be archived by WCTU; trial data generated at sites will be archived according to local policy.

### Confidentiality {27}

The University of Warwick is the Sponsor for the trial. The trial is being conducted in full adherence with the principles of the Declaration of Helsinki and MRC Good Clinical Practice principles and guidelines. It also complies with all applicable UK legislation and Warwick Standard Operating Procedures. All data are being stored securely and held in accordance with the Data Protection Act 2018. All identifiable data are pseudonymised and treated as confidential. All CRFs, questionnaires, trial reports and communication regarding the trial will identify the participants by the assigned unique trial identifier only. Participant confidentiality will be maintained at every stage and identifiable information will not be made publicly available.

### Plans for collection, laboratory evaluation and storage of biological specimens for genetic or molecular analysis in this trial/future use {33}

Not applicable, no biological specimens collected.

## Statistical methods

### Statistical methods for primary and secondary outcomes {20a}

All statistical analyses will be undertaken on an intention to treat basis where possible to preserve randomisation, avoid bias from exclusions and preserve statistical power. Hence, all participants randomised into the trial, regardless of whether they received their randomised intervention, will be analysed according to their randomised group using data collected up to their final follow-up in the trial (6-month timepoint or the last timepoint prior to their withdrawal or loss to follow-up). We will do an additional per-protocol analysis including only participants who received their allocated intervention (as detailed in the statistical analysis plan). Participants not receiving surgery or withdrawing consent for follow-up prior to surgery will not be included in relevant denominators.

For the primary outcome of DAH30, each randomised treatment arm’s point estimate (and 95% confidence interval) will be reported. In addition, DAH30 will be compared across randomised treatment arms using independent samples *t*-tests, Wilcoxon rank sum tests or appropriate modelling techniques depending on the distribution of the data. The secondary outcome of DAH90 will be analysed as per the DAH30 techniques. Rates of mortality and major post-operative complications will be assessed across randomised arms using chi-squared tests, with logistic regression used to adjust for stratification variables.

Quality of recovery, participant satisfaction and accidental awareness will be scored using appropriate manuals.

The four stratification factors used at randomisation define sub-groups of interest.Surgical speciality* (intrabdominal/musculoskeletal/thoracic/vascular/other)Expected duration of surgery (< 2 h, ≥ 2 h)*Cancer surgery/non-cancer surgery*Preoperative frailty (Rockwood frailty score*)—well/vulnerable/frail [45]

A Consolidated Standards of Reporting Trials (CONSORT) flow diagram will be produced, showing the frequency of participants:Assessed for eligibilityExcluded prior to randomisation (and the frequency of each reason for exclusion)RandomisedAllocated to each randomisation armReceiving or not receiving their randomised treatmentFollowed-up at each protocol specified timepointLoss to follow-up at each protocol specified timepoint (and the frequency of each reason for loss to follow-up)

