### Sample size {14}

The total sample size will be 2500 participants over the two intervention arms (1250 per arm). The primary endpoint of this trial is the number of days alive and at home 30 days after surgery (DAH30). DAH30 is a continuous number between 0 and 30 which reflects, out of the 30 days following surgery, the total number of those days that a participant spends alive and at home [43]. In this definition, home reflects any place other than hospital. If a participant dies within those 30 days, their value is set to 0. The secondary endpoints of this trial include number of days alive and at home 90 days after surgery (DAH90) and survival at 90 days after surgery. The population eligible for entry into VITAL is similar to those participants undergoing elective surgery reported by Bell in 2019 with a mean DAH30 of 25 (SD 6.6) [44]. Applying the VITAL trial inclusion and exclusion criteria to sample data using hospital episode statistics, we found a mean DAH90 of 72.9 (SD 21.3) and a 90-day mortality rate of 3.8%. We have adopted a conservative estimate of 7.5 for the standard deviation of DAH30 and a conservative estimate of 22 for the standard deviation of DAH90. With a 5% two-sided significance level and 90% power, the randomisation of 2500 participants (1:1) to either TIVA or inhalational anaesthesia would allow detection of a difference of 1 day in DAH30 between treatment arms. This sample size allows for up to 5% loss-to-follow-up. Also, with a 5% two-sided significance level, this 2500 participant sample will allow us to detect a difference in DAH90 between arms of 3 days with 90% power, or 4 days, with > 95% power. For a safety non-inferiority analysis of 90-day mortality, assuming there is truly no difference between modes of anaesthesia (3.8% mortality), a 2500 participant sample would provide 80% power for a one-sided 95% confidence interval to exclude a 1.9% increase in mortality due to TIVA (a relative risk of 1.5). A one-sided 97.5% confidence interval would exclude an increase due to TIVA of 2.2% (a relative risk of 1.6).

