## Assignment of interventions: allocation

### Sequence generation {16a}

Participants will be randomised on a 1:1 basis to receive either TIVA or inhalational anaesthesia. Randomisation will be undertaken through a simple and secure, Interactive Voice Response Randomisation System (IVRS) that has been established by the programming team at Warwick Clinical Trials Unit. This computerised procedure will use a minimisation algorithm to ensure balance in treatment arm allocation across the following four stratification variables, factors thought to affect outcome either through treatment effectiveness or underlying prognosis, also permitting appropriate exploratory subgroup analyses:Surgical speciality (musculoskeletal/intra-abdominal/thoracic/vascular/other)Expected duration of surgery (< 2 h, ≥ 2 h)Cancer surgery/non-cancer surgeryPreoperative frailty (Rockwood frailty score)—well/vulnerable/frail [45]

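### The two tests named for DAH30 and DAH90 leave out the four minimisation factors, so if used they are conservative and give up a little power

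*Protocol article*

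**What the plan says.** Under Sequence generation {16a}, the protocol article allocates 1:1 with a "minimisation algorithm to ensure balance in treatment arm allocation across the following four stratification variables, factors thought to affect outcome". The factors are surgical speciality (five levels), expected duration (two), cancer or non-cancer surgery (two) and frailty (three). Hospital is not among them.

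Under Statistical methods for primary and secondary outcomes {20a}, "DAH30 will be compared across randomised treatment arms using independent samples" t-tests, Wilcoxon rank sum tests, or some suitable model, with the choice left to the distribution of the data. No covariates are named for that model. DAH90 is to be handled in the same way. For mortality and major complications, the same section names chi-squared tests, "with logistic regression used to adjust for stratification variables".

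Linear regression for DAH30 and DAH90 is mentioned only under Methods for additional analyses {20b}, for the exploratory subgroups.

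**The concern.** Minimisation forces the arms to be alike on the four factors. The part of DAH30 that those factors explain then contributes almost nothing to the chance difference between the arm means. A two-sample test does not know this: its standard error still contains that part of the variance. The analysis therefore claims more uncertainty than the design leaves. Confidence intervals come out too wide, p-values too large, and some of the precision bought by the allocation method is lost.

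The article recognises the principle for mortality and complications but does not carry it to the outcome on which the trial was sized. The open third option does not settle the matter, because it is triggered by the shape of the data and not by the design.

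**Working it through.** **Inputs from the article (Sample size {14}).** Two-sided 5% level, 90% power, 1250 per arm; a "conservative estimate of 7.5 for the standard deviation of DAH30"; the sample "would allow detection of a difference of 1 day in DAH30 between treatment arms"; and "This sample size allows for up to 5% loss-to-follow-up".

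**Input not in the documents.** R2, the share of DAH30 variance explained by the four factors. It is assumed here to lie between 0.02 and 0.20.

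**Step 1: reproduce the stated sample size, with no adjustment.**
n per arm = 2 × (1.960 + 1.282)² × 7.5² / 1² = 1183 (rounded up), so 2366 in total. Allowing 5% loss: 2366 / 0.95 = 2491, against 2500 stated. The figure reproduces.
After 5% loss there are 1250 × 0.95 = 1187.5 per arm. SE = 7.5 × sqrt(2/1187.5) = 0.308 days, and power = Φ(1/0.308 − 1.960) = 90.1%.

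**Step 2: the unadjusted t-test when the factors are balanced by design.** Let s = sqrt(1 − R2). The true standard deviation of the difference is s × SE, but the test uses SE.
- True two-sided level = 2 × (1 − Φ(1.960/s))
- Power of the unadjusted test = Φ((1/SE − 1.960)/s)
- Power of the adjusted test = Φ(1/(s × SE) − 1.960), with its level at 5%
- Excess width of the unadjusted interval = 1/s

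Worked case, R2 = 0.10: s = 0.949. Level = 2 × (1 − Φ(2.066)) = 3.9%. Unadjusted power = Φ(1.289/0.949) = 91.3%. Adjusted power = Φ(3.249/0.949 − 1.960) = 92.9%.

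| Assumed R2 | True level, unadjusted | Power, unadjusted | Power, adjusted | Gain (points) | Interval width ratio |
|---|---|---|---|---|---|
| 0.02 | 4.8% | 90.4% | 90.7% | 0.3 | 1.01 |
| 0.05 | 4.4% | 90.7% | 91.5% | 0.8 | 1.03 |
| 0.10 | 3.9% | 91.3% | 92.9% | 1.6 | 1.05 |
| 0.15 | 3.4% | 91.9% | 94.1% | 2.2 | 1.08 |
| 0.20 | 2.8% | 92.5% | 95.3% | 2.8 | 1.12 |

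**Step 3: check by simulation.** The formulas assume perfect balance, which minimisation only approaches. Minimisation was simulated on factors with 5, 2, 2 and 3 levels, with 2376 participants and an assumed 80% probability of the balancing arm (2500 replicates under no effect, 1000 under a 1-day effect).

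| Scenario | Level, unadjusted | Level, adjusted | Power, unadjusted | Power, adjusted |
|---|---|---|---|---|
| R2 0.05 | 4.4% | 4.9% | 90.4% | 91.2% |
| R2 0.10 | 4.5% | 5.6% | 90.8% | 91.6% |
| R2 0.20 | 3.2% | 5.2% | 92.9% | 96.2% |
| R2 0, hospital effect 5% of variance | 5.2% | 5.2% | 91.6% | 91.8% |

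The simulation standard error is about 0.4 points for a level near 5% (sqrt(0.05 × 0.95/2500)) and about 0.9 points for a power near 92% (sqrt(0.92 × 0.08/1000)). The direction agrees with the formulas throughout. In the last row, where only hospital matters and hospital is not balanced by design, the unadjusted level stays at about 5%.

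**The case against.** The strongest reply is that the article does not rule out adjustment. Its third option would admit a regression on the four factors, the same section refers to a statistical analysis plan that is not shown here, and the covariates of a primary model are commonly fixed there. This stands to the extent that one cannot say the plan ignores the factors. It does not remove the point: the article names two specific tests for its primary outcome, both unadjusted, and makes the alternative depend on the data distribution.

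The contrast with the binary outcomes should also not be pressed too far. Unadjusted chi-squared tests are named first for those, and the article does not say whether they or the adjusted logistic model come first.

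The size is modest and rests on an assumed R2. At R2 of 0.05 or less the gain is under 1 point of power. The figures are for the t-test; none was computed for the Wilcoxon test.

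Three stronger readings are tempting and not supported. A reader might infer that the 5% level is exceeded; every level calculated for the unadjusted test after balancing on prognostic factors is below 5%, so there is no added false-positive risk. A reader might infer that leaving out hospital also distorts the standard error; hospital is not a minimisation factor, and the hospital-only simulation shows no such effect. A reader might infer that the trial is underpowered without adjustment; the stated sample size reproduces, and unadjusted power is at least 90% throughout.

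**Conclusion.** The point holds in a limited form. The independent-samples t-test and the Wilcoxon test, as named for DAH30 and carried over to DAH90, do not reflect the allocation method that the same article describes. If the t-test is used, its standard error is too large by about 1/sqrt(1-R2). For R2 from 0.02 to 0.20 this means a true level of about 4.8% to 2.8%, an interval about 1% to 12% wider than needed, and a loss of about 0.3 to 3 points of power. These figures assume near-perfect balance on the factors, the article's SD of 7.5, a 1-day difference and 5% loss. DAH90 is affected in the same way, according to its own R2. This is a loss of efficiency and a mismatch between design and analysis; it does not threaten the validity of a positive result.

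**What to change.** Pre-specify the primary analysis of DAH30, and that of DAH90, as a linear regression on arm plus the four minimisation factors, with robust standard errors. Report the adjusted mean difference in days with its 95% confidence interval as the primary result, and the unadjusted comparison as supportive. Do not let the choice between adjusted and unadjusted analysis depend on the observed distribution. Adjusting for hospital is optional: it could add precision but is not needed to correct the standard error.

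The cost is a sentence or two in the statistical analysis plan, or a confirmation if that plan already says so. The four factors are recorded for every participant at randomisation. They use eight degrees of freedom (4 + 1 + 1 + 2) out of roughly 2,400. No change to recruitment, follow-up or data collection is involved. The article plans no interim analysis and keeps results by arm from the management group and steering committee during the trial, so the model can be fixed before the arms are compared.

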### Health economic evaluation

A prospectively planned economic evaluation will be conducted from an NHS and personal social services perspective, according to the recommendations of the NICE reference case [46]. Use of resources during the index admission, where change can be attributed to anaesthesia, will be captured by PQIP. These will include time in surgery and length of stay by level of care. Participants’ community contacts, made in connection with their surgery, will be recorded in the first 6 months. Participants will be encouraged to use an electronic or paper calendar to help recall this information at follow-up. Healthcare resource use will be costed using most recently available published national reference costs, reflated to the most recent year [47]. We will describe reported resource use disaggregated, providing hospital and community usage time horizons. We will simplify resource collection as much as possible, preparing participants to understand the resource information sought and promoting this recording through diaries.

Generic health-related quality-of-life will be assessed at baseline, at discharge, 30 days and at 6 months using the EQ-5D-5L questionnaire. EQ-5D-5L scores will be converted to health status scores using the UK value set recommended by NICE guidance at the time of analysis [48, 49]. Participant-level QALY estimates will be estimated as the area under the curve (AUC) of health status scores over time using the trapezoidal rule. Baseline EQ-5D-5L will be included to minimise bias in the QALY calculation and to adjust subsequent analyses [50, 51]. Whilst a greater number of observations would undoubtedly be desirable, the measurement schedule is necessarily pragmatic within the design of the trial. Varying time to discharge may possibly be a proxy for achieving an adequate quality-of-life. Longer hospital stay increases the contribution of the hospital period to the overall AUC and decreases the contribution of the post-discharge period, as both are time-weighted; hence, the (informatively) varying discharge timepoint should provide a more accurate QALY estimate than a fixed point, because it better characterises the shape of the AUC. We will perform a sensitivity analysis omitting the discharge point as a check for consistency of findings. We will monitor levels of missingness of resource and outcome data, taking steps to promote quality of reporting.

Within-trial analysis (to 6 months) using bivariate regression of costs and QALYs will inform a probabilistic assessment of incremental treatment cost-effectiveness [52]. Mechanisms of missingness of data will be explored and multiple imputation methods will be applied to impute missing data [53–55]. Imputation sets will be used to estimate incremental cost per QALY estimates and confidence intervals. Findings will be analysed and visualised in the cost-effectiveness plane, as cost-effectiveness acceptability curves, net monetary benefit and value of information analysis (EVSI). Should costs and quality-of-life not converge within 6 months, more extensive economic modelling using decision-analytic methods may be considered to extend the target population, time horizon and decision context, drawing on best available information from the literature and stakeholder consultations to supplement the trial data. Parameter uncertainty in the decision-analytic model will be explored using probabilistic sensitivity analysis. If longer term decision modelling is to be undertaken, then costs and outcomes will be discounted at 3.5% after the first year of randomisation in line with NICE reference case [46]. Analyses and modelling will be undertaken in Stata 16 SE (or later release if available). Reporting will follow the Consolidated Health Economic Evaluation Reporting Standards (CHEERS) statement [56].

### Interim analyses {21b}

There are no planned interim analyses.

### Methods for additional analyses (e.g. subgroup analyses) {20b}

Pre-specified sub-group analyses will be undertaken using appropriate modelling techniques. These will be determined following examination of the distributions of the collected data but are anticipated to be linear regression for DAH30 and DAH90 and logistic regression modelling for mortality rates at 90 days. These exploratory sub-group analyses will have lower power than the main whole trial analysis but are hypothesis-generating, and results will be scrutinised graphically via forest plots.

### Methods in analysis to handle protocol non-adherence and any statistical methods to handle missing data {20c}

Every effort will be made to collect full baseline, treatment and follow-up data on all trial participants; it is thus anticipated that missing data will be minimal. Participants with missing primary outcome data will not be included in the primary analysis in the first instance. This presents a risk of bias, and sensitivity analyses will be undertaken to assess the possible impact of the risk. This will consist of simulating the missing responses using a multiple imputation approach.

